**Methods::**

We aimed this protocol to evaluate the quantitative/qualitative characteristics of the salivary flow in healthy volunteer subjects (n = 20) and in subjects suffering from common OC pathologies (n = 40), before and after 7 days of supplementation with SaliflussTM (Metis Healthcare srl, Milan, Italy), a Class I medical device on the market as 400 mg mucoadhesive oral tablets that has Car as the main ingredient.

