## Aim of the study

2

The main objectives of this protocol are to estimate the quantity/quality of oral salivae and OM in healthy volunteers and in subjects affected by common OD, before and after 7 days of treatment with Salifluss^TM^, 1 tablet twice a day. The characteristics of oral saliva (Sal) that will be studied are (a) unstimulated and stimulated (paraffin-activated) salivary flow rates and pH and (b) quantitative proteomics (QP), on selected targets, representing the main proteins/components of OM.

By matching Sal characteristics with OM and comparing them with OD, we do expect to elucidate their mutual relationship; furthermore, using specific bioinformatics tools to analyze the data, before and after treatment with Car, we are looking to see its potentials on preventing/treating OD and, using QP, eventually elucidate the mechanism of action.

The study will take place at the Odontoiatric University Clinic (OUC), Istituto Stomatologico Italiano (ISI) of Milan, Italy, in a prospective, randomized, double-blind, and placebo-controlled fashion.

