### Sampling

3.2

Since the study is focused on saliva samples, subjects with severe hypo-salivation at the first sampling (saliva flow rate at baseline <0.1 mL min^−1^), because of their inability to dissolve the tablet formulation, will be rolled out. Saliva production will be determined by the spit method at baseline (*t* = 0) and after 7 days of treatment (*t* = 1) with Salifluss^TM^ twice a day or placebo.

The participants will be asked to avoid oral hygiene practices including flossing, brushing, and mouth-rinses as well as eating, and drinking for at least 2 hours before collection. Before sampling, the mouth will be rinsed with water for 2 minutes, and the subject will be asked to wait for 10 minutes.

The saliva samples will be obtained in the morning (8.00 am–10.00 am) according to the circadian rhythms in salivary flow.^[11]^ The unstimulated saliva samples will be collected by expectorating into sterile 50 mL tubes every 30 seconds. for 5 minutes as described earlier.^[12]^ The stimulated saliva will be collected in the same way after 2 minutes of chewing a paraffin wax ball.

The samples collected by an operator unaware of clinical data will be weighted, the pH will be measured by a pH-sensitive electrode, then centrifuged at 5000 *g* for 10 min at 4°C; the obtained supernatants will be supplemented with EDTA-free Protease Inhibitor Mixture (Sigma–Aldrich, Dorset, UK) and stored al −80° for the QP analysis. The collected samples will be analyzed at the Department of Pharmaceutical Sciences “Pietro Pratesi,” University of Milan, Milan, Italy (DISFARM) research laboratory.

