### Administration of Car

3.3

Subjects understudy will be instructed to assume Salifluss^TM^ twice a day, in the morning and before bedtime. Salifluss^TM^ is a Class I medical device according to EU Dir. no 93/42/CE (as amended by EU Dir. No. 2007/47/CE), notified to Italian Ministry of Health with ID number 1810197/1810202. At recommended doses, the intake quantities of the substances meet the requirements and limitations set by the Italian Ministry of Health. As previously introduced, Salifluss^TM^ is a 400 mg mucoadhesive oral tablet (13 × 4 mm^2^) with smooth surfaces whose main ingredient is Car. The tablet should be placed in the gingival fornix and, thanks to its mucoadhesiveness, let to dissolve slowly. The dissolution time of the tablet is around 2 hours in normal salivation conditions. Placebo tablets, similar to Salifluss^TM^ ones, will be administered to randomly selected n = 20 subjects, 10/10 from Cs/Ds. An SMS reminder will be sent to all the subject reminding to take the pill.

Patients will be encouraged to report any adverse events and other unintended effects of trial interventions.

Attached the technical and safety data sheets, the certificate of analysis, and the sell-sheet of the extract of Cr.

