### Statistical analysis

3.5

Descriptive statistics of continuous variables understudy will be presented as mean ± SD; categorical variables were expressed as absolute numbers and percentages. The differences in continuous variables will be assessed using the Mann–Whitney *U* test when not normally distributed, and the Student *t* test when normally distributed. The *X*^2^ test was used to test for differences in categorical variables. The relationship between all variables before and after active/placebo treatment will be tested by Spearman correlation coefficients and their 95% confidence intervals.

The primary outcome variable is the treatment-related change in any of the Sal parameter understudy, before and after active/placebo treatment in Cs/Ds subjects by intention to treat criteria, that is, including all patients with adequate sampling before and after treatment (7 days). Differences in treatment-related changes between the groups will be analyzed in the context of covariance analyses (ANCOVA), which included terms for treatment and baseline values as covariates. Treatment effects were assessed by the least-squares mean change from the above ANCOVA model.

If relevant, the intra- and inter-observer variability of sampling, as well as measurements, a repetition of sampling and data analysis will be performed. For intra-observer variability the primary observer will sample/analyze the data on 2 different days; for inter-observer variability the sample/analysis will be performed, independently, by a second observer who was blinded to previous results. Intra- and inter-observer variability will be calculated as the coefficient of variance, which is the standard deviation of the difference between observations divided by their mean and multiplied by 100.

The size of the sample and the power will be calculated expecting a type I error rate of 5% or less. When appropriate, a value of *P* < .05 will be considered significant.

If samples are missing for any cause (eg, not compliance with the trial protocol, no follow-up, others) they will be removed from the analysis.

Data will be analyzed at the end of the study when all samples will be collected. Access to the data in anonymized mode will be provided to the investigators.

A computer statistical package will be used to validate the model and to perform the analysis (SPSS v.20, IBM, Armonk, New York, USA).

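### The primary analysis is labelled intention to treat but is defined as a complete-case set: only subjects with adequate samples at both baseline and day 7

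*Protocol article*

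**What the plan says.** The Aim section describes a trial run in a "prospective, randomized, double-blind, and placebo-controlled fashion". Section 3.5 (Statistical analysis) opens its account of the primary outcome with "The primary outcome variable is the treatment-related change in any of the Sal parameter understudy", and states that this is analysed "by intention to treat criteria, that is, including all patients with adequate sampling before and after treatment (7 days". The article thus supplies its own definition of intention to treat.

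Later in section 3.5 the missing-data rule reads: "If samples are missing for any cause (eg, not compliance with the trial protocol, no follow-up, others) they will be removed from the analysis". The model is given as "covariance analyses (ANCOVA), which included terms for treatment and baseline values as covariates".

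Saliva is collected "at baseline (*t* = 0) and after 7 days of treatment (*t* = 1"), so there is one follow-up measurement. The article describes no other analysis set, no imputation and no sensitivity analysis for missing samples, and it does not say what makes a sample adequate.

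**The concern.** Intention to treat means that subjects are analysed in the arm to which they were randomised, whatever happens afterwards. The set in section 3.5 depends on two things that happen afterwards: returning at day 7, and giving a sample judged adequate. A subject who fails either leaves the primary analysis. The comparison is then no longer between the groups that randomisation formed, and a reader of the results would be told that it was.

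The undefined word adequate adds a specific risk. Salivary flow rate is one of the parameters under study, so a small day-7 collection is a result. If it were judged inadequate, the subject would be removed because of the outcome value. Nothing in the article prevents this. The hypo-salivation rule in section 3.2 applies only to the first sampling and says nothing about day 7.

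The placebo arm is small, so a few removals could matter.

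**Working it through.** **1. The label against the definition.** The plan states no dropout rate, SD, effect size or power figure for this analysis, so there is no figure to reproduce. The check is a comparison of the text.

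- Label: intention to treat.
- Definition: adequate samples at both time points.
- Missing-data rule: missing samples are removed, whatever the cause.

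A randomised subject without an adequate day-7 sample is left out under both the definition and the rule. The ANCOVA is therefore run on complete cases.

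**2. Group sizes.** The abstract gives "healthy volunteer subjects (n = 20) and in subjects suffering from common OC pathologies (n = 40"), 60 in all. Section 3.3 says that placebo "will be administered to randomly selected n = 20 subjects, 10/10 from Cs/Ds". By subtraction:

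- placebo: 10 healthy + 10 diseased = 20;
- active: (20 − 10) + (40 − 10) = 10 + 30 = 40.

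**3. Shift in one arm's mean (illustration).** Let *r* of *n* subjects be removed, let the retained mean be *m*, and assume that the removed subjects' mean change is 1 SD worse. Then

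full-arm mean = (1 − r/n)·m + (r/n)·(m − 1 SD) = m − (r/n) SD,

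so the retained mean is too high by r/n SD.

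| Removed from placebo | Within one group, n = 10 | Pooled, n = 20 |
|---|---|---|
| 1 | 0.10 SD | 0.05 SD |
| 2 | 0.20 SD | 0.10 SD |
| 3 | 0.30 SD | 0.15 SD |

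The stated ANCOVA has terms for treatment and baseline only, which suggests pooling, but the text does not settle whether healthy and diseased subjects are analysed together. Both columns are therefore shown.

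**4. From one arm to the contrast.** These are shifts in one mean. Under the same 1 SD assumption, losing 2 of 20 on placebo and 4 of 40 on active shifts each mean by 0.10 SD, and the difference is unbiased: 0.10 − 0.10 = 0.

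At the other extreme, suppose that only the active arm loses subjects, 5% to 20% of them, with changes 0.5 to 1 SD lower than those kept. The contrast is then biased by 0.05 × 0.5 = 0.025 SD to 0.20 × 1 = 0.20 SD. Take a normal approximation, unit SD and a two-sided 5% test (the article does not state sidedness).

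- Lower end: 38 active remain, SE = √(1/20 + 1/38) = 0.276, and bias/SE = 0.025/0.276 = 0.09. Type I error is about 5.1%.
- Upper end: 32 active remain, SE = √(1/20 + 1/32) = 0.285, and bias/SE = 0.20/0.285 = 0.70. Type I error is Φ(−1.96 + 0.70) + Φ(−1.96 − 0.70) ≈ 0.104 + 0.004, or about 10.8%.

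**5. Would a mixed model rescue the excluded subjects?** Not here. With one follow-up value and a common covariance, the likelihood factorises as f(y₀)·f(y₁ | y₀, arm). In a baseline-constrained model the second factor has mean μ₁ + δ·arm + β(y₀ − μ₀), so δ is the ANCOVA treatment coefficient. A subject with only y₀ contributes to the first factor alone and so informs the baseline mean and variance but not δ. The maximum-likelihood estimate of δ equals that of the complete-case ANCOVA.

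**The case against.** The strongest defence is that this is an available-data analysis with a loose label. Follow-up is 7 days with one return visit, and section 3.3 provides SMS reminders, so losses may be few. No analysis can use a day-7 value that was never obtained without making assumptions. This stands as a limit on the likely size of the problem. It does not make the definition intention to treat.

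Three stronger readings are tempting, and the documents do not support them.

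- **A reader might infer that non-compliers are excluded, as in a per-protocol set.** The rule removes missing samples and names non-compliance as one reason why a sample may be missing. It does not exclude a subject who took few tablets but gave both samples, and no one is moved out of the assigned arm.
- **A reader might infer that low-flow subjects are the likeliest to be dropped.** The article does not say so. Section 3.2 has samples weighed after a timed 5-minute collection, so a low flow can be measured, and subjects below 0.1 mL/min at the first sampling are already excluded. Only the weaker statement holds: with adequate undefined, such a subject could be dropped.
- **A reader might take 0.1 to 0.3 SD as the bias in the treatment effect.** It is the shift in one arm's mean within one group of 10, under an assumed 1 SD gap. It halves on pooling and shrinks if the other arm loses subjects too.

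It may also be said that an article leaves such matters to the full plan. That would cover silence, but here the article states an analysis set and a missing-data rule that contradict its own label.

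**Conclusion.** The point holds as a contradiction between label and definition: the primary analysis is complete-case on a set selected after randomisation. No other section repairs it, and the undefined term adequate leaves room for removal that depends on the outcome.

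The consequence cannot be sized from the documents. The shifts in the placebo mean (0.1 to 0.3 SD within a group, 0.05 to 0.15 SD pooled) rest on 1 to 3 removals and a 1 SD gap. The type I error range of about 5.1% to 10.8% rests on losses in the active arm only. All of these are assumptions, and balanced losses would bring the bias towards zero. The direction is also open: losing poor responders from placebo understates a benefit, and losing them from active overstates it.

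This should be fixed, though it does not invalidate the design. The Discussion says that the study has not started, so the change can be made before any data exist.

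**What to change.** In section 3.5:

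1. Define the target set as all randomised subjects, analysed in their assigned arm.
2. State that the day-7 sample is sought at the planned visit whatever the tablet compliance.
3. Define adequate, and record a low-volume day-7 collection as a measured low flow. This helps the flow outcomes only; it cannot supply a missing pH or proteomic value.
4. Call the ANCOVA on subjects with both samples complete-case, and report losses by arm and reason.
5. Add a sensitivity analysis that departs from missing at random, such as delta-adjusted multiple imputation by arm and group. Fix the deltas in advance and vary them separately by arm. Three of the four arm-by-group cells hold only 10 subjects, so the imputation model must be simple.

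Do not rely on a baseline-constrained mixed model to bring in subjects with only a baseline sample. With one follow-up it returns the complete-case ANCOVA estimate, and ordinary multiple imputation under missing at random does not address outcome-dependent loss either.

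The cost is wording in section 3.5 and modest extra analysis. No extra subjects or scheduled visits are needed.

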### Subjects selection

3.1

Among subjects referring to the OUC, we will enroll, on a voluntary basis, n = 40 diseased subjects (Ds), aged 18–40 years having at least 1 of the following OD: (a) dental erosions, (b) caries, and (c) périodontopathies, for example, gingivitis or aggressive/chronic periodontitis.

The criteria for each OD were defined on the basis of commonly accepted grading scores in dentistry. Dental erosions will be counted; for caries, we will adopt the missing and filled dental criteria; for périodontopathies, we will record the probing depth, clinical attachment loss, plaque index, and bleeding on probing using a manual periodontal probe.

A complete medical and dental history will be obtained from all participants; all the volunteers must not present allergies/intolerances to the consumption of Car or take other food supplements or any type of drug treatment (interview). Exclusion criteria will be also smoking, pregnancy/lactation, and the presence of any systemic diseases such as cardiovascular and respiratory, diabetes mellitus, HIV infection, or inflammatory conditions causing non-plaque dependent OD. Patients eligible for the study will return to the OUC after being pre-screened. Before being enrolled in the study, participants will provide written and informed consent for use of their saliva samples and clinical data for scientific research purposes. The study is in accordance with the guidelines of the World Medical Association Declaration of Helsinki.

A control group (Cs) of 20 age-matched subject with periodontal health will be enrolled among the staff of the OUC. The number of subjects identified and considered sufficient for the research is based on a preliminary test conducted on the salivary flow obtained from the staff involved in the project. The schedule of enrolment, interventions, and assessments, and the flow-chart of the protocol are depicted in Figures 1 and 2.

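### Placebo is allocated 1:1 in controls but 3:1 active to placebo in diseased subjects, and the primary ANCOVA lists no disease-group term, so a pooled fit would be open to confounding by disease status

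*Protocol article*

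**What the plan says.** Three parts of the protocol article bear on this.

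- **Group sizes (Subjects selection, 3.1).** The diseased group is "n = 40 diseased subjects (Ds), aged 18–40 years". The comparison group is described as "A control group (Cs) of 20 age-matched subject with periodontal health".
- **Allocation (Administration of Car, 3.3).** Placebo tablets "will be administered to randomly selected n = 20 subjects, 10/10 from Cs/Ds". Under Aim of the study (2), the trial is to run in a "prospective, randomized, double-blind, and placebo-controlled fashion".
- **Analysis (Statistical analysis, 3.5).** The primary outcome is the change in saliva parameters "before and after active/placebo treatment in Cs/Ds subjects by intention to treat criteria". Between-group differences in change are analysed by an ANCOVA "which included terms for treatment and baseline values as covariates", and the treatment effect is the least-squares mean change from that model.

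The article does not list a Cs/Ds term or a treatment-by-group term. It also does not say whether the model is fitted once to everyone or once in each group.

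**The concern.** Placebo numbers are fixed at 10 in each group, but the groups differ in size, so the active-to-placebo ratio is 1:1 in Cs and 3:1 in Ds. When the probability of active treatment depends on a stratum, randomisation protects the comparison within each stratum. A comparison across strata is protected only if the analysis accounts for the stratum.

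A model with treatment and baseline alone, fitted to all 60 subjects, does not do that. Suppose the saliva of diseased subjects moves differently over seven days from that of controls with the same starting value, whatever tablet they take. Part of that difference would then be credited to treatment, or set against it, depending on its sign. The imbalance is designed in, so recruiting more subjects at the same ratios would not remove it. At stake are the estimate and the error rate of the primary active-placebo comparison.

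**Working it through.** **1. Reproduce the allocation.** Inputs are 40 Ds and 20 Cs (section 3.1) and placebo "randomly selected n = 20 subjects, 10/10 from Cs/Ds" (section 3.3). The placebo total is 10 + 10 = 20, as stated. The active numbers follow by subtraction.

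| | Active | Placebo | Total | Chance of active |
|---|---|---|---|---|
| Cs | 10 | 10 | 20 | 50% |
| Ds | 30 | 10 | 40 | 75% |
| Total | 40 | 20 | 60 | |
| Share diseased | 30/40 = 75% | 10/20 = 50% | | |

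**2. Bias of a pooled fit, by omitted-variable algebra.** Let T = 1 for active, D = 1 for diseased, and let d be the Ds-minus-Cs difference in 7-day change at equal baseline and treatment. If D is left out, the treatment coefficient is biased by a × d, where a is the coefficient of T when D is regressed on the terms that are in the model.

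- Var(T) = Var(D) = (2/3)(1/3) = 0.2222.
- Cov(T, D) = 30/60 − (2/3)(2/3) = 0.0556.
- *Equal group baselines:* a = 0.0556 / 0.2222 = 0.25, which is also 75% − 50%.
- *Group baselines 1 SD apart (assumed; within-group SD 1):* Var(B) = 1 + 0.2222 = 1.2222. In absolute value Cov(B, D) = 0.2222 and Cov(B, T) = 0.0556, both with the same sign. Then a = (0.0556 × 1.2222 − 0.0556 × 0.2222) / (0.2222 × 1.2222 − 0.0556²) = 0.0556 / 0.2685 = 0.21.

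The bias is therefore about 0.25 × d in the first case and about 0.2 × d in the second. It is zero if d = 0.

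**3. Type I error, by simulation.** The documents give no value for d, so d is an assumed range in residual SD units. Set-up: 60 subjects in the fixed layout above, no true treatment effect, baseline slope −0.5, residual SD 1, two-sided 5% test (the protocol does not state sidedness), 8,000 runs per case. The model contained treatment and baseline only.

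| d | Bias, equal baselines | Type I error | Bias, 1 SD baseline difference | Type I error |
|---|---|---|---|---|
| 0 | 0.00 | 5.0% | 0.00 | 5.0% |
| 0.5 | 0.13 | 6.8% | 0.11 | 6.2% |
| 1.0 | 0.25 | 10.0% | 0.20 | 7.9% |
| 1.5 | 0.37 | 14.6% | 0.31 | 12.2% |

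Repeat simulations put the largest figure at about 14-15%. At d = 0.25 the error is about 5-5.5%.

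**4. The same cases with a Cs/Ds term added.** The bias is about 0 and type I error is 4.6-5.3% throughout.

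**5. Cost in precision.** The standard error of the treatment contrast, in residual SD and ignoring baseline, is:

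- without the group term: √(1/40 + 1/20) = 0.274;
- with the group term: within-group precisions are 1/(1/10 + 1/10) = 5 for Cs and 1/(1/30 + 1/10) = 7.5 for Ds, so the standard error is √(1/12.5) = 0.283.

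The ratio is 0.283 / 0.274 = 1.03, an increase of about 3%.

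**The case against.** **Pooling is not stated.** The primary outcome refers to both groups and placebo is fixed within each, so an ANCOVA run separately in Cs and in Ds is an open reading. Under that reading treatment plus baseline is a sound model. Simulated at d = 1.5 SD with a 1 SD baseline difference, bias is about 0 and type I error is 5.0% in Ds and 5.3% in Cs. This stands, and it makes the point conditional on a pooled fit. It does not remove the point, because the text does not select that reading and a reader who pools all 60 is following the words as written.

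**The size may be small.** The protocol expects saliva to be altered in oral disease. That concerns levels, and the baseline covariate absorbs most of a difference in level. For d of 0.1-0.3 SD the simulated error is 4.7-5.7%. Measurement noise alone can make d non-zero, since each group regresses toward its own mean. With stable group levels 0.5-1 SD apart and reliability 0.6-0.9 (both assumed), bias is at most 0.08 SD and the error 4.6-6.1%. With wider assumptions (levels 0.5-2 SD apart, test-retest correlation 0.4-0.8), bias is 0.02-0.16 SD and the error about 5-8%. This also stands: double-digit error rates need a d of about 1 SD or more, and nothing in the documents supports or excludes that.

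**This is a condensed article, and the list of terms need not be complete.** An article may leave stratification factors to the analysis plan. Here, however, the article does name the terms of its primary model, and that list does not fit its own allocation. The point concerns what is stated.

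**Conclusion.** The listed terms of the primary ANCOVA do not match the unequal allocation. If the model is fitted to all 60 subjects, the active-placebo contrast carries a bias of about 0.2 to 0.25 × d, and a nominal 5% test has a true type I error between 5% and about 14-15% for d between 0 and 1.5 residual SD. The range of d and the 1 SD baseline difference are assumptions; the allocation figures are the protocol's own.

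Three stronger conclusions might be inferred, and the documents do not support them.

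- *That the trial's randomised comparison is biased by construction.* Subjects are randomised within Cs and within Ds, so two valid randomised comparisons exist. The pooled contrast is biased only if d is not zero.
- *That the model makes a flawed comparison of Cs with Ds, adjusting a non-randomised contrast on a noisy baseline.* This depends on another reading of an ambiguous phrase about differences between groups. The listed term is treatment, not disease group.
- *That a treatment-by-group interaction must be the test of differential response.* The protocol states no such hypothesis, and with cells of 10, 10, 10 and 30 the test would have low power.

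The point should be fixed. It is a specification gap in the primary analysis with a very cheap remedy, not a fatal flaw.

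**What to change.** Amend section 3.5 in one of two ways.

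- **Add the group.** State that the primary ANCOVA contains treatment, disease group (Cs/Ds) and the baseline value. This costs one sentence, one degree of freedom and about 3% in the standard error. No extra subjects or data are needed. The pooled estimate then weights the groups by precision, 5/12.5 = 0.4 for Cs and 7.5/12.5 = 0.6 for Ds, apart from baseline adjustment.
- **Or analyse by group.** State that the ANCOVA with treatment and baseline is run separately within Cs and within Ds. This also removes the bias, but each comparison is less precise: the standard error is √(1/10 + 1/10) = 0.447 residual SD in Cs and √(1/30 + 1/10) = 0.365 in Ds, against 0.283 for the combined model. The protocol should then say which of the two comparisons is primary.

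A treatment-by-group term may be reported as a secondary analysis. The Discussion says the study has not started, so either change can be made before any data are seen.

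### The observer-variability index in section 3.5 cannot show a constant difference between observers and is not interpretable for pH, so poor reproducibility could be reported as a small percentage

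*Protocol article*

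**What the plan says.** The check is conditional. Section 3.5 (Statistical analysis) opens it with "If relevant, the intra- and inter-observer variability of sampling, as well as measurements". For the intra-observer part, "the primary observer will sample/analyze the data on 2 different days". For the inter-observer part, "the sample/analysis will be performed, independently, by a second observer who was blinded to previous results".

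Both parts are summarised in the same way: "Intra- and inter-observer variability will be calculated as the coefficient of variance", defined as "which is the standard deviation of the difference between observations divided by their mean and multiplied by 100". No mean difference, limits of agreement or intraclass correlation is named beside it. No limit separates acceptable from poor reproducibility, and no decision is tied to the result.

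The formula makes no exception for any measure. Section 2 (Aim of the study) lists the saliva characteristics as "unstimulated and stimulated (paraffin-activated) salivary flow rates and pH", with proteomics besides. Section 3.5 builds the primary outcome on them: "The primary outcome variable is the treatment-related change in any of the Sal parameter understudy". pH is therefore both a primary measure and one to which the index would be applied.

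**The concern.** A second observer, blinded to the first set of readings, is brought in largely to learn whether two people working independently get systematically different values. The standard deviation of the paired differences does not contain that information. Add a constant to every reading of one observer and it does not move.

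The second problem concerns pH only. A coefficient of variation needs a scale with a true zero. Flow rate has one. pH is a logarithm, its zero is arbitrary, and dividing by a number near 7 makes any error look small.

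At stake is how a published reproducibility figure is read. A low percentage may be taken as reassurance about a primary saliva measure when the index could not have shown the disagreement, or when the scale guaranteed a low value.

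**Working it through.** The article states no variability figure, so there is none to reproduce. The check applies its formula to model readings.

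**Inputs.** From section 3.5: index = 100 × SD(difference) / mean, with the mean taken as that of the observations. Assumed, because the article gives no values: mean pH 7.0; between-subject SD 0.3 (range 0.2 to 0.5); error SD 0.1 per reading; offset b of 0, 0.3 or 0.5 pH; mean flow 0.4 mL/min with error SD 0.03.

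**Model.** Observer A reads true value + error. Observer B reads true value + b + error. Then:

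- SD(difference) = √2 × error SD, whatever b is.
- Mean of the observations = mean + b/2.
- Absolute-agreement ICC = between-subject variance / (between-subject variance + error variance + b²/2).
- 95% limits of agreement = b ± 1.96 × SD(difference).

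**1. Constant offset, pH.** SD(difference) = √2 × 0.1 = 0.141.

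| Offset b (pH) | Index | ICC (agreement) | Limits of agreement (pH) |
|---|---|---|---|
| 0 | 0.141/7.00 = 2.0% | 0.09/0.10 = 0.90 | −0.28 to 0.28 |
| 0.3 | 0.141/7.15 = 2.0% | 0.09/0.145 = 0.62 | 0.02 to 0.58 |
| 0.5 | 0.141/7.25 = 1.9–2.0% | 0.09/0.225 = 0.40 | 0.22 to 0.78 |

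The index stays put while agreement falls by more than half.

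**2. Constant offset, flow.** SD(difference) = √2 × 0.03 = 0.042. With no offset the index is 0.042/0.40 = 10.6%. With an offset of 0.2 mL/min, half the mean, it is 0.042/0.50 = 8.5%. It improves because the offset enlarges the denominator. A within-subject CV that includes the offset, √(mean squared difference / 2) / mean, goes from 7.5% to about 29%.

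**3. Proportional offset, flow.** If the second observer collects 20% more from everyone and there is no random error, the index is 0.2 × between-subject CV / 1.1. That is 5.5%, 9.1% and 12.7% for between-subject CVs of 0.3, 0.5 and 0.7. The difference is understated but not removed.

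**4. The pH scale.** Let the error SD equal the between-subject SD, so that ICC = 0.50. The index is √2 × SD / 7:

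- SD 0.2: 4.0%
- SD 0.3: 6.1%
- SD 0.5: 10.1%

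At SD 0.3, one SD of the difference is 0.424 pH, and 10^0.424 = 2.7, so a 2.7-fold difference in hydrogen-ion concentration is shown as about 6%.

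**5. The other reading of the denominator.** The wording could also mean the mean of the differences. With error SD 0.1, the index is then 0.141/0.3 = 47% at an offset of 0.3 and 0.141/0.5 = 28% at 0.5, and it is unbounded as the offset approaches zero. These figures are not small, but they fall as the observers move apart.

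**The case against.** The strongest objection is that little depends on this paragraph. The check is optional, no threshold labels a percentage good or poor, and the figure enters no other analysis. A reader might infer that poor reproducibility *would* be reported as good, or that unresolvable pH changes would be accepted as treatment effects. The document supports neither. The treatment effect comes from a baseline-adjusted ANCOVA in a randomised, placebo-controlled comparison. Random pH error widens its standard error whatever percentage is printed. A constant observer offset tends to cancel between arms unless observers are unevenly spread across them, and nothing in the article indicates that they are. This part of the objection stands and limits the point to what the index *could* hide.

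The index is also not biased downwards in every respect. For purely random error it is √2 times a standard within-subject CV, about 41% larger (2.0% against 1.4%). At error SD 0.3 a within-subject CV for pH would be 0.3/7 = 4.3%, smaller than the 6.1% above. That is true, but it confirms that the pH scale is the problem, and it does nothing for blindness to an offset.

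Section 3.2 has pH read by electrode and samples weighed, so readings are instrumental, and nothing in the article suggests an offset as large as 0.5 pH. This stands: the offsets are illustrations. That the index ignores a constant offset in its numerator is algebra and needs no assumption.

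Finally, the percentage need not be the only output. Section 3.5 plans means and tests of differences for continuous variables, which would reveal an offset if applied to the repeat readings. The text does not say that they will be. Nor is this mere detail left to a fuller document, since the article itself fixes the formula.

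**Conclusion.** The point holds in a limited form, as a low-severity improvement. If the check is done, and the denominator is the mean of the observations, the index cannot show a constant difference between observers, for flow or for pH. For pH it is also not interpretable as a percentage. The scale objection does not apply to flow, which is a ratio measure.

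Under the assumed values, a 0.5 pH offset leaves the index near 2% while agreement ICC drops from 0.90 to 0.40, and error equal to the between-subject spread reads as about 6% (4% to 10% for SDs of 0.2 to 0.5). The ICC values depend on the assumed between-subject SD. The alternative reading of the denominator does not rescue the index. The ANCOVA treatment comparison is unaffected.

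**What to change.** Change the wording in section 3.5:

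- Define the denominator as the mean of all paired observations, and keep the percentage for flow only.
- For pH, report the within-subject SD, or the SD of the paired differences, in pH units, and say which.
- For inter-observer comparisons of flow and pH, add the mean difference with its 95% CI and the 95% limits of agreement. For flow, give these as ratios from the log scale, so that a proportional difference is shown directly.

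The Discussion says that the study has not started, so the wording can still be changed. The cost is a few extra lines of analysis on the same repeat readings, with no further samples or subjects. The reported reproducibility may look less favourable.
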